### Study Setting

This study will be conducted entirely online; participants will complete the intervention (mindfulness program) in real-world (and, thus, ecologically valid) settings. Participants will be recruited and will communicate with the research team online. All data collection will be completed via their mobile phone, PC, or tablet.

### Eligibility Criteria

Participants who provide written informed consent and meet the inclusion and exclusion criteria provided in Textbox 1 will be eligible for the study.

Inclusion and exclusion criteria.
**Inclusion criteria**
Age of 18 to 64 years (working-age adults as specified by the Australian Bureau of Statistics)Residence in Australia, with no overseas relocation or travel plans that would impact the ability to participate in the study (ie, engage with meditation practices or receive and respond to surveys)Sufficient comprehension of the English language to complete measuresRegistration for an account and agreement to the terms and conditions of Unforgettable.me, a web platform administered by Unforgettable Research Services Pty LtdIf experiencing anxious or depressive symptoms of moderate severity (defined by a score of >19 on the Patient-Reported Outcomes Measurement Information System [PROMIS] Anxiety Short Form or >22 on the PROMIS Depression Short Form), agreement to continue the recommended routine medical treatment for eligible underlying mental or physical health conditions for the duration of the study and to seek additional treatment if indicated by deterioration of symptomsSuccessful completion of the run-in periodNo or minimal experience with meditation, defined as <25 hours over the previous 6 months, and having never attended a multiday mindfulness course (eg, mindfulness-based stress reduction or Vipassana meditation). If we have not recruited 50% of our target sample size within the first 3 months of active recruitment, we will broaden the inclusion criteria to participants with up to 100 hours of mediation experience in the previous 6 months
**Exclusion criteria**
Self-reported current or lifetime serious mental illness (eg, neurodevelopmental, schizophrenia spectrum, bipolar, obsessive-compulsive, trauma-related, dissociative, or personality disorder)Anxious and depressive symptoms in the severe range (defined by a score of >27 on the PROMIS Anxiety Short Form or >32 on the PROMIS Depression Short Form)Psychological distress symptoms in the severe range (Kessler Psychological Distress Scale ≥30)Threshold scores on prescreening and follow-up measures exceeded for mania, suicidal ideation, psychosis, repetitive thoughts and behaviors, and dissociationModerate or higher alcohol, tobacco, or drug useSelf-reported diagnosis of a neurological condition (eg, traumatic brain injury, amnesia, epilepsy, or stroke)Self-reported presence of any serious medical condition (eg, cancer, thyroid disorder, or multiple sclerosis)Recent bereavement or major lossHistory of unexplored, untreated traumatic experiences or adverse childhood events

The selection criteria will be self-assessed. Throughout the study, we will conduct various checks to verify the accuracy of the information provided in the prescreening survey to determine study eligibility. Participants whom we suspect provided inaccurate information may be required to verify specific details. If we cannot verify such information within 1 week, that participant will be deemed to have responded inaccurately and excluded from the study. Although we will make every effort to flag and remove inauthentic participants before randomization (ie, during the run-in period), in some cases, it may not be possible and, therefore, removal will take place after randomization. The Assignment of Interventions: Allocation and Blinding section provides details on how we will handle postrandomization exclusion.

Details on the procedure that we will use to flag and remove inauthentic participants were preregistered but are being kept confidential from study participants to avoid influencing behavior or actions that could compromise the procedure. Accordingly, the exact methodology has been embargoed [22] and will only be disclosed after data collection closes.

### Prescreening Measures

Individuals will complete a prescreening survey to determine their eligibility.

*Sociodemographic* questions will consist of items related to age and gender. Supplementary sociodemographic questions will be asked on day 1 of the run-in period, comprising questions about ethnicity, household status, indigenous status, and education status.

*English proficiency* will be assessed by asking whether the primary language spoken is English. Participants for whom English is not their primary language will be asked whether they have sufficient proficiency to complete the study given that all study materials are in English.

*Residency and location* during the study will be assessed by asking whether the participant resides in Australia; whether they intend to travel outside Australia during the following 5 weeks; and, if so, whether such travel is likely to affect their participation.

*Mental health status* will be measured using the *Diagnostic and Statistical Manual of Mental Disorders, Fifth Edition*, Self-Rated Level 1 Cross-Cutting Symptom Measure [23], a 23-item self-report measure designed to assess symptoms across 13 domains of mental health. We will measure 5 of the 13 domains: mania, suicidal ideation, psychosis, repetitive thoughts and behaviors, and dissociation. We will administer level 2 follow-up measures (Table 1) in cases in which scores for any level 1 domain exceed clinical cutoffs. For depression and anxiety, level 2 measures will be administered in lieu of the relevant level 1 items. Additional screening measures will include (1) the Kessler Psychological Distress Scale, for anxiety and depressive symptoms; (2) a single-item measure of substance use within the last year that, if any item is endorsed, will trigger a more detailed drug and alcohol screening questionnaire; and (3) a single-item measure of trauma that, if endorsed, will trigger a more detailed trauma screening questionnaire. Endorsement of any item on the more detailed screener will trigger a brief questionnaire to screen for posttraumatic stress disorder.

*Meditation history* will ask individuals whether they have practiced meditation in the past and, if so, to select the types of meditation they have practiced and total estimated practice time in the previous 6 months and since commencing.

The other selection criteria will be determined by asking participants directly (eg, a question about recent bereavement).

**Table 1 table1:** Follow-ups to prescreening measures if the threshold score is exceeded.

Domain of interest	Measure	Criteria	Description
Mania	ASRM^a^	Raw score>10^b^, indicating high probability of manic or hypomanic condition	The ASRM is a 5-item measure that assesses mood, self-confidence, sleep disturbance, speech, and activity level [24].
Suicidal ideation	DSI-SS^c^	Total score>2	The DSI-SS is a 4-item measure that assesses the frequency and intensity of suicidal ideation, formulation of plans for suicide, the controllability of suicidal thoughts, and impulses related to suicide.
Psychosis	PQ-16^d^	Total score>5	The PQ-16 is a 16-item measure of psychosis with 9 items on perceptual abnormalities and hallucinations, 5 items on unusual thought content, and 2 items on negative symptoms.
Repetitive thoughts and behaviors	Repetitive Thoughts and Behavior	Average score of >2 (total raw score ≥11), indicating severe or extreme symptoms	Repetitive Thoughts and Behavior is a 5-item assessment of repetitive thoughts and behaviors that has been adapted from the FOCI^e^ Severity Scale.
Dissociation	DES-B^f^-Modified	Average score of >2 (total raw score ≥17), indicating severe or extreme symptoms	The DES-B-Modified is an 8-item assessment of the severity of dissociative experiences [25].
Substance use	NIDA^g^ Quick Screen (version 1.0), NIDA-Modified ASSIST^h^, and AUDIT^i^ alcohol screening tool	See the “Description” column	We will ask participants whether they have used alcohol (≥5 drinks for men and ≥4 drinks for women), tobacco, prescription drugs for nonmedical reasons, or other illegal drugs in the past year. If the participant endorses “once or twice” or more frequent use in the last year, we will ask which drugs and additionally ask about frequency of use in the past 3 months (“never,” “once or twice,” “monthly,” “weekly,” “daily,” or “almost daily”). For alcohol, participants reporting daily use (of 5 drinks for men and 4 drinks for women) will be excluded. Participants reporting weekly or monthly use will be administered the alcohol screening tool, and a score of ≥14 will result in the participant being excluded. For tobacco, participants reporting daily use will be excluded. For drugs (prescription drugs for nonmedical reasons or illegal drugs), participants reporting weekly or daily use will be excluded. If participants report monthly use or use once or twice, we will ask additional questions as follows: (1) “In the past three months, how often have you had a strong desire or urge to use [drug]? How often has your use of [drug] led to health, social, legal, or financial problems? How often have you failed to do what was normally expected of you because of your use of [drug]?” (2) “Have you ever tried and failed to control, cut down, or stop using [drug]?” (response options: “no” and “yes”). For drugs other than cannabis, if monthly or more frequent use is reported for any of the 3 items from question 1 or the participant answers “yes” within the last 3 months for question 2, they will be excluded. For cannabis, if weekly or more frequent use is reported for any of the 3 items from question 1 or the participant answers “yes” within the last 3 months for question 2, they will be excluded.
Trauma	Single-item measure of trauma history and BTQ^j^	The BTQ is administered if the item is endorsed. Endorsement of any item on the BTQ will trigger assessment of PTSD^k^ (see the following row)	We will ask participants to respond to the following item: “Sometimes things happen to people that are unusually or especially frightening, horrible, or traumatic. For example, a serious accident or fire; a physical or sexual assault or abuse; an earthquake or flood; seeing someone be killed or seriously injured; having a loved one die through homicide or suicide. Have you ever experienced this kind of event?” (response options: “yes” and “no”). If the participant answers “yes,” the BTQ will be administered. The BTQ is a 10-item measure to ascertain whether the respondent has experienced a traumatic event, which includes experiences of potentially traumatic events such as crime and sexual and physical assault [26]. Endorsement of any item on the BTQ will trigger an assessment of PTSD (refer to the following row).
PTSD	PCL-5A^l^	Endorsement of any item indicates probable PTSD	The PCL-5A is a 5-item measure used to screen for the presence of PTSD.

^a^ASRM: Altman Self-Rating Mania Scale.

^b^The exclusion threshold for the ASRM was updated from >5 to >10 as of March 12, 2025, after it became apparent that the original threshold was too sensitive, excluding a higher-than-expected number of participants. A subsequent review of the literature confirmed that the ASRM has low specificity in nonclinical populations [27], supporting the decision to revise the threshold. The updated threshold was applied retrospectively, and individuals who had been excluded under the previous criterion but scored ≤10 were invited to recomplete the prescreening questionnaire.

^c^DSI-SS: Depressive Symptom Index–Suicidality Subscale.

^d^PQ-16: 16-item Prodromal Questionnaire.

^e^FOCI: Florida Obsessive-Compulsive Inventory.

^f^DES-B: Brief Dissociative Experiences Scale.

^g^NIDA: National Institute on Drug Abuse.

^h^ASSIST: Alcohol, Smoking, and Substance Involvement Screening Test.

^i^AUDIT: Alcohol Use Disorders Identification Test.

^j^BTQ: Brief Trauma Questionnaire.

^k^PTSD: posttraumatic stress disorder.

^l^PCL-5A: abbreviated Posttraumatic Stress Disorder Checklist for the Diagnostic and Statistical Manual of Mental Disorders, Fifth Edition.

### Interventions

#### Active Condition With Varied Doses

This study will include 3 active conditions that are dose variants of a newly developed 28-day mindfulness meditation program. The program is based on the *Satipatthana Sutta* (*The Discourse on the Establishing of Mindfulness* [28]—a foundational text within the Vipassana or insight tradition of Theravada Buddhism on which MBPs such as mindfulness-based stress reduction are largely based [29]). Most empirical work in the field of meditation has been conducted in the context of MBPs. The program generally aligns with the definition of an MBP developed by Crane et al [30]. The *Satipatthana Sutta* is structured into 4 progressive “contemplations”: body, feelings, mind, and “dhammas” or mental qualities [28]. This program will feature daily instructions and guided practices that are based on the first 3 contemplations: the body, feelings, and the mind.

The program has been developed independently by Australian meditation teacher [name] with support from Australian meditation teacher [name] based on specifications (ie, number of sessions, session length and duration, and intended audience) but with limited additional input from the research team. [name] has practiced meditation within the insight tradition since 1977 and has been teaching meditation full time for the past 20 years.

All 3 variants of the program will feature the same structure, progression, and content but will vary in length of daily teaching and practice: 10, 20, and 30 minutes. Each program consists of an introduction, practice, and conclusion. While the introduction and conclusion are consistent across the 3 programs, longer sessions include more practice points. Additional practice points in the longer sessions represent elaborations on content already introduced rather than new themes. In total, each 10-minute session includes 5 practice points, each 20-minute session includes 10 practice points, and each 30-minute session includes 15 practice points. The proportion of time allocated to spoken content varies across the 3 programs accordingly, from 62% for the 10-minute sessions to 47% for the 20-minute sessions and 40% for the 30-minute sessions.

Practices will be provided for 6 days each week (ie, a total of 24 guided practices), with participants given the option to practice without guidance on the seventh day. Each variant will teach the same core content; however, the longer variants will have more time to elaborate on this content through teaching and gain experience practicing the guided techniques.

Practice instructions will consist of a brief explanation of relevant theory as well as a set of instructions for the practice in the first few minutes, followed by intermittent guided instructions throughout the duration of the practice. The programs will consist entirely of prerecorded material and will be delivered asynchronously. Therefore, there will be no direct contact between teachers and participants for the duration of the program. While this element constitutes a point of departure from how most MBPs are delivered, Crane et al [30] note that the exact method of delivery is flexible and can vary across MBPs [31].

After the 28-day intervention period, participants will be offered full access to any of the 3 higher-dose courses that they choose. During this time, participants will be free to choose to engage as much or as little with the guided practices as they wish.

#### Minimal-Dose Control Condition

The minimal-dose condition will feature a short daily meditation approximating 4 minutes (akin to the breathing space practice in mindfulness-based cognitive therapy or short practices in popular meditation apps). This condition is intended to provide a brief introduction to the foundations of mindfulness in theory and practice and follows the same course structure as the 3 active conditions. However, due to time constraints, the content will be very superficial.

### Outcomes

#### Overview

*Personality* will be measured on days 2 and 3 of the run-in period using the short form of the Big Five Inventory, a 30-item measure of personality across 5 domains: open-mindedness, conscientiousness, extraversion, agreeableness, and negative emotionality [32].

*Sleep* will be assessed on day 4 of the run-in period using a single item from the Sleep Quality Scale [33]: “During the past week, how would you rate your sleep quality overall?” (response options: *terrible*=1, *poor*=2-4, *fair*=5-7, *good*=7-9, and *excellent*=10).

*Motivations and expectancy* will be measured on day 4 of the run-in period using the following questions: (1) “How much benefit do you expect from this mindfulness meditation course?” (response options: not at all to very much), (2) “What is your main goal for completing this mindfulness meditation course?” (goal or motivation free-text field), (3) “How motivated are you by this goal?” (response options: not at all to very much), (4) “How much improvement or progress toward your goal do you expect from the course?” (response options: none at all to a great deal), and (5) “How confident are you that the amount of improvement or progress you indicated will occur?” (response options: not confident at all to extremely confident).

The outcome measures in the following paragraphs will be obtained at baseline (T0) and the midintervention (T0.5) and postintervention (T1) time points and after a 1-month follow-up period (T2) unless otherwise indicated.

*Psychological well-being (primary outcome)* will be assessed at T0, T1, and T2 using the Warwick-Edinburgh Mental Wellbeing Scale (WEMWBS) [34], which includes 14 positively worded items of mental well-being for the previous 2 weeks on a 5-point Likert scale from 1 (none of the time) to 5 (all of the time). The primary outcome measurement is at T1. Previous analyses of responsiveness to change analyses indicate that the WEMWBS detects individually meaningful improvement across a variety of mental health measures [35]. These analyses indicated an average SE of measurement over time of 2.69.

*Psychological distress (secondary outcome)* will be assessed at T0, T0.5, T1, and T2 using the Kessler Psychological Distress Scale [36], a 10-item self-report measure of psychological distress over the previous month, on a 5-point Likert scale from 1 (none of the time) to 5 (all of the time).

*Anxiety (secondary outcome)* will be assessed at T0, T0.5, T1, and T2 using the Patient-Reported Outcomes Measurement Information System (PROMIS) Anxiety Short Form [37], a 7-item measure of the pure domain of anxiety over the previous 7 days, on a 5-point Likert scale from 1 (never) to 5 (always) and the anxiety subscale of the Depression, Anxiety, and Stress Scale [38], a 7-item measure of anxiety over the previous 7 days that is assessed on a 4-point Likert scale from 0 (did not apply to me at all—never) to 3 (applied to me very much or most of the time).

*Depression (secondary outcome)* will be assessed at T0, T0.5, T1, and T2 using the PROMIS Depression Short Form [37], an 8-item measure of depression over the previous 7 days, on a 5-point Likert scale from 1 (never) to 5 (always).

*Social anxiety (secondary outcome)* will be assessed at T0 and T1 using the Social Anxiety Disorder Severity Scale [39], a 10-item measure of the severity of symptoms of social anxiety (phobia) in the previous 7 days, on a 5-point Likert scale from 0 (never) to 4 (all of the time).

*Nonattachment (secondary outcome)* will be assessed at T0, T0.5, T1, and T2 using the Nonattachment Scale [40], which measures the Buddhist concept of nonattachment on a 5-point Likert scale from 1 (disagree strongly) to 5 (agree strongly).

*Trait mindfulness (secondary outcome)* will be assessed at T0, T0.5, T1, and T2 using the Five Facet Mindfulness Questionnaire [41,42], a 15-item measure that includes 5 factors representing elements of mindfulness, on a 5-point Likert scale from 1 (never or very rarely true) to 5 (very often or always true).

*Decentering (secondary outcome)* will be assessed at T0, T0.5, T1, and T2 using the Experiences Questionnaire [43,44], an 11-item measure of decentering, on a 5-point Likert scale from 1 (never) to 5 (all the time).

*Equanimity (secondary outcome)* will be assessed at T0, T0.5, T1, and T2 using the Two-Factor Equanimity Scale [45], a 14-item measure of equanimity, on a 5-point Likert scale from 1 (never) to 5 (very often or always).

*Repetitive negative thoughts (secondary outcome)* will be assessed at T0, T0.5, T1, and T2 using the Repetitive Negative Thoughts Questionnaire [46], a 22-item measure of repetitive negative thinking, on a 6-point Likert scale from 1 (not at all typical of me) to 6 (extremely typical of me).

*Emotion regulation (secondary outcome)* will be assessed at T0, T0.5, T1, and T2 using the Difficulties in Emotion Regulation Scale–Short Form [47], an 18-item measure that includes 6 factors representing emotional regulation problems, on a 5-point Likert scale ranging from 1 (almost never) to 5 (almost always).

*Attention control (secondary outcome)* will be assessed at T0, T0.5, T1, and T2 using the Attention Control Scale–Short Form [48], a 10-item measure that includes 2 subscales of attention (shifting and focusing), on a 4-point Likert scale ranging from 1 (almost never) to 4 (always).

*Emotional reactivity (secondary outcome)* will be assessed at T0, T0.5, T1, and T2 using the Perth Emotional Reactivity Scale–Short Form [49], an 18-item measure of the activation, intensity, and duration of one’s emotional responses, on a 5-point Likert scale from 1 (very unlike me) to 5 (very like me).

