**Methods:**

At least 688 healthy adults aged between 18 and 65 years will be randomized to join one of three 4-week online mindfulness courses with daily practices of varying lengths (ie, 10, 20, or 30 min) against a minimally active control condition (4 min). Psychological well-being will be measured using the Warwick-Edinburgh Mental Wellbeing Scale at the baseline, midintervention, and postintervention time points and at 1-month follow-up. Secondary outcomes are psychological distress, anxiety, depression, social anxiety, nonattachment, trait mindfulness, decentering, equanimity, repetitive negative thoughts, emotion regulation, attention control, and emotional reactivity. Other outcomes will be collected weekly and daily during the intervention period. The primary analysis will be undertaken following the intention-to-treat approach. We will also conduct per-protocol secondary analyses on all outcomes (ie, primary and secondary). In addition, we will systematically monitor for possible adverse experiences.

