#### Effectiveness Analyses

A constrained longitudinal data analysis method [57] will be used to build the linear mixed-effects model estimating the effect of the interventions on the primary outcome. The model will incorporate study visit (T0 and T1) as a categorical variable, intervention (10, 20, and 30 min each vs the minimal dose), and intervention by study visit interaction as main effects. The model will assume a common baseline mean of the outcome across the 4 intervention groups and an unstructured variance-covariance among the repeated measurements.

Models analyzing secondary outcomes will incorporate study visit (T0, T0.5, and T1) and intervention (10, 20, and 30 min each vs the minimal dose) as categorical variables. Secondary continuous outcomes will be analyzed similarly to the primary outcome (ie, the constrained longitudinal data analysis described previously). Additional analyses will include follow-up assessments (ie, T2) in the model.

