#### Missing Data Handling

As the primary strategy to handle missing data, the longitudinal constrained analysis assumes that the probability of missing outcome data is not related to the missing data but to some of the observed measured data in the model (missing at random). Our models will use a restricted maximum likelihood estimator to handle missing data. The use of the restricted maximum likelihood estimator will enable us to effectively handle the potential bias introduced by differential attrition as it allows for the estimation of unbiased fixed-effects coefficients and appropriately accounts for the variability introduced by random effects.

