#### Sensitivity Analysis

The frequency and percentage of participants with missing data at T0, T0.5, T1, and T2 will be summarized for the primary and secondary outcomes. In addition, baseline and demographic characteristics will be summarized for those with and without missing data for the primary outcome measure (at T0, T0.5, T1, and T2) to explore the missing data assumption and identify and include in the relevant models any variables not included in the target primary analysis that are potentially associated with missingness.

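### The protocol disagrees on whether the primary outcome is measured midintervention, and its assurance about differential attrition is too strong for a primary model that uses T0 and T1 only

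*Protocol article*

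**What the plan says.** All references are to the protocol article.

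- **Abstract, Methods:** the WEMWBS is measured "at the baseline, midintervention, and postintervention time points and at 1-month follow-up".
- **Outcomes, Overview:** the default schedule is T0, T0.5, T1 and T2, with the last "after a 1-month follow-up period (T2) unless otherwise indicated". The primary outcome then "will be assessed at T0, T1, and T2 using the Warwick-Edinburgh Mental Wellbeing Scale (WEMWBS"). T0.5 is left out, and T1 is named as the primary time point.
- **Effectiveness Analyses:** for the primary outcome, "The model will incorporate study visit (T0 and T1) as a categorical variable". For the others, "Models analyzing secondary outcomes will incorporate study visit (T0, T0.5, and T1").
- **Efficacy Analyses:** one per-protocol model with T0, T0.5 and T1 is described for all outcomes, the primary included.
- **Missing Data Handling:** missing at random is assumed given observed data in the model, and restricted maximum likelihood "will enable us to effectively handle the potential bias introduced by differential attrition".
- **Sensitivity Analysis:** baseline and demographic characteristics are to be compared for those "with and without missing data for the primary outcome measure (at T0, T0.5, T1, and T2"), and variables associated with missingness are to be added to the relevant models.

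**The concern.** There are two linked problems.

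First, a reader cannot tell whether the primary outcome is collected at T0.5. This concerns the schedule of the primary endpoint, so it is not a detail that can be left to an analysis plan.

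Second, with visits T0 and T1 only, a participant without T1 enters the likelihood through the baseline score alone. Nothing that happened after randomization informs the missing value. If people leave one dose arm more often than another, and those who leave have responded differently in the first two weeks, the estimated T1 means are shifted by different amounts and the dose contrast is biased. The protocol nevertheless asserts that the estimator deals with differential attrition, and its check for predictors of missingness names only baseline and demographic characteristics. Retention by dose is one of the trial's own objectives, so the assurance matters.

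**Working it through.** **1. The schedule, side by side**

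| Section | T0.5 for the WEMWBS? |
|---|---|
| Abstract, Methods | yes |
| Outcomes, Overview | no (T0, T1, T2) |
| Effectiveness Analyses, primary model | not used |
| Efficacy Analyses, all outcomes | yes, but generic wording |
| Sensitivity Analysis, primary outcome named | yes |

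The abstract and the Sensitivity Analysis section cannot both stand with the Outcomes section. The per-protocol sentence is weaker evidence. The equally generic sentence for secondary outcomes also lists T0.5, although social anxiety is measured only at T0 and T1. The timeline figure was not in the text available for this check.

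**2. The plan's own sample size**

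Inputs from Sample Size: SD 9.84, r = 0.83, difference 1.97, two-sided alpha 0.02, power 80%.

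- Post-score only: 2 × [9.84 × (2.326 + 0.842) / 1.97]² = 501 per arm.
- Change-score factor: 2(1 − 0.83) = 0.34, giving 171 per arm and 684 in total, against the stated 172 and 688.
- Dropout: 688 / 0.80 = 860, as stated.

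The plan's figures reproduce on one baseline and one post measure. Nothing below changes the sample size.

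**3. Where the two-visit model is sound**

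Large simulation: true effect 1.97 at T1 and half of that at T0.5, r = 0.83 between all visits, dropout 10% in the low-dose arm and 30% in the high-dose arm.

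- Dropout depends on arm only: estimate 1.96.
- High-dose dropout depends on baseline WEMWBS: estimate 1.98.

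Both recover 1.97 within simulation error.

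**4. Where it is not**

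Assume the odds of dropout rise by a factor of 1.5, 2 or 3 per SD lower T0.5 score given baseline. The arm-specific rates and odds ratios are assumptions. The protocol gives only about 80% retention overall.

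| Dropout, low vs high dose | Two-visit estimate or bias | Share of 1.97 |
|---|---|---|
| 10% vs 30% | 2.17, 2.27, 2.40 (bias 0.20 to 0.43) | 10% to 22% |
| 15% vs 25% | bias 0.11 to 0.21 | 6% to 11% |
| 20% vs 20%, same mechanism | 1.96 to 1.98 | about zero |

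Hand check of the middle case (odds ratio 2, 10% vs 30%):

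- SD of T0.5 given T0: 9.84 × √(1 − 0.83²) = 5.49.
- Slope of T1 on T0.5 given T0: 0.83 / 1.83 = 0.454. One residual SD at T0.5 is therefore worth 0.454 × 5.49 = 2.49 points at T1.
- Mean residual among those who stay: ln 2 × E[p(1 − p)] / (1 − p̄), where E[p(1 − p)] ≈ p̄(1 − p̄) − [p̄(1 − p̄) ln 2]².
- High dose: 0.693 × 0.189 / 0.70 = 0.187. Low dose: 0.693 × 0.086 / 0.90 = 0.066.
- Bias: (0.187 − 0.066) × 2.49 = 0.30, which matches 2.27 − 1.97.

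Reversing the sign of the slope, so that people who feel better leave, reverses the sign of the bias.

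A steeper mechanism, with dropout linked to early well-being or early change in the high-dose arm only and log-odds slopes of 0.5 to 2 per SD, gives 2.16 to 2.89.

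**5. What T0.5 would add**

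If T0.5 is observed for everyone randomized, the three-visit estimate is 1.96 to 1.97 in the 10% vs 30% case. If half of the dropouts also miss T0.5, it is 2.04, 2.08 and 2.14. If 90% do, it is 2.13, 2.22 and 2.33, which is little correction.

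**6. Scale**

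The standard error of a contrast at 172 per arm, adjusted for baseline, is 5.49 × √(2/172) = 0.59. A bias of 0.20 to 0.43 is 0.3 to 0.7 standard errors; 0.11 to 0.21 is 0.2 to 0.4.

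**The case against.** The strongest reply is that the protocol predicts lower adherence at higher doses, not more missing T1 scores. Strengths and Limitations treats dropout and adherence separately, and Participant Compensation pays for surveys whether or not the person meditates. Someone who stops practising but answers at T1 is not missing under intention to treat. Only one retention figure is given, and bias from differential attrition is called potential. This stands: dose-related dropout is a possibility the plan allows for, not one it forecasts.

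The size and direction of any bias also rest on assumed inputs. A reader might infer that it favours higher doses and so the first hypothesis. Nothing in the document shows who would leave.

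Nor is a midintervention score a full remedy. It helps only those who leave after T0.5, and only under missing at random. Run-In Period cites about 90% of app attrition within the first seven days. The run-in should absorb part of that, but later dropout cannot be presumed.

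Finally, if the Outcomes section is right, a T0 and T1 model simply fits the data collected, and the Sensitivity Analysis section does provide for adding variables associated with missingness. That is fair as to the choice of model. It does not resolve the conflicting schedule. It also does not rescue the attrition claim, because the only predictors named for that check are baseline and demographic, and they do not capture early response.

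**Conclusion.** The schedule conflict is established from the text alone and needs no assumption. The statement about differential attrition is too strong for the stated primary model. It holds when T1 missingness depends on arm and baseline WEMWBS, and fails when dropout differs by arm and also tracks early response.

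A reader might go further and infer that the model cannot handle dose-related dropout at all. The calculations do not support that: dropout driven by dose alone, or by dose and baseline well-being, leaves the contrast unbiased.

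Under the stated assumptions the bias is about 0.2 to 0.4 points with 10% versus 30% dropout and 0.1 to 0.2 points with 15% versus 25%. It takes the opposite sign if those who feel better leave, and is about zero if dropout is equal across arms. This is modest beside a standard error of 0.59, but not negligible against a 1.97-point target. The point should be corrected. It does not invalidate the design or the sample size.

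**What to change.** 1. Reconcile the abstract, Outcomes, Efficacy Analyses and Sensitivity Analysis with what the live T0.5 survey contains.
2. If the WEMWBS is in that survey, add T0.5 to the primary constrained longitudinal model and keep the T1 contrast as primary.
3. If it is not, correct the other sections and add a sensitivity analysis for T1 WEMWBS that uses post-baseline data already planned: T0.5 distress, anxiety and depression scores, and the weekly practice reports.
4. In either case, limit the claim in Missing Data Handling to dropout explained by variables in the model. State that T0.5 data reduce bias only for participants who leave after T0.5, and only under missing at random.

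The cost is some rewording and one or two extra model runs. No new visits or measures are needed, and the sample size does not change.
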